#### Double-blind randomization and allocation concealment

Enrolled patients undergoing aortic surgery will be divided randomly into a control group (ANH) and an aPRP group using a computer-generated sequence. Groups will be chosen before patient admission, and all patients and staff will be oblivious to their group assignment. The anesthesiologist will not be informed of the patient assignments, which are recorded and sealed in sequentially numbered opaque envelopes. Nurse anesthetists can give sealed envelopes and tell to prepare the items for the experiment based on group allocations; there are no differences in the look of the two sets of envelopes. The group assignment will be withheld from all patients and anesthesiologists. Following anesthesia induction, the anesthesiologist may perform the various surgeries in accordance with the coded number. Another anesthesiologist will document intraoperative data and followed up on the patient’s discharge. Finally, the data will be analyzed by a professional statistician.

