### aPRP collection

aPRP will be collected from a large-bore central venous access via gravity drainage, with approximately 15–20 mL/kg whole blood collected prior to heparin administration. The collected whole blood will be divided into aPRP and red blood cells using an autologous transfusion system (Sorin Electa Essential; Sorin, Italy). The target yield of aPRP is 10 mL/kg. The amount of PRP collected can be determined using kilogram mass, and most research [2, 11] specify a collection of 10 mL/kg of aPRP, with the exception of the 1994 study [12], which collected 15 mL/kg of aPRP.

Specific steps: An anticoagulation prefilled blood collection tube is connected to an external central venous access for blood collection. The anticoagulant solution is maintained at a constant drop to mix with the blood in the tube, and the blood entering the centrifuge chamber is centrifuged to separate aPRP and RBCs. While the blood is being drained, a crystalloid solution is infused through the peripheral vein to maintain hemodynamic stability. Blood collection was stopped when the target volume was reached. All blood collection, extraction and other operations required strict asepsis, and the resulting aPRP was stored inter-operatively at room temperature under shaking conditions. The whole separation and extraction process is completed before CPB heparinization. The aPRP will then be stored in sodium citrate collection bags at room temperature (usually 22~24 °C). When extracorporeal circulation is stopped, collected whole blood is inserted in a blood bag containing sodium citrate and transfused, heparin is neutralized with ichthyoglobulin, and no active bleeding is detected throughout operation. The anesthesiologist decided to perform aPRP.

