### Data collection and management

Dedicated staff will record all data and complete a case report form for each patient. Relevant demographic characteristics and the patients’ past medical histories, including age, height, weight, and diagnosis, will be collected at the time of patient inclusion. Intraoperative data, including mean arterial pressure, heart rate, oxygen saturation, and central venous pressure, will be recorded before the beginning and after the end of collection and before and after the return infusion. TEG testing will also be performed before and after the collection and before and after the return infusion. The decision to use blood products such as fibrinogen, prothrombin complex, coagulation factors, and platelets will be made based on the TEG results.

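### The trial is called double-blind, but the anesthesiologist and operating-room staff cannot be blinded to two visibly different techniques

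*Protocol article*

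**What the plan says.** The abstract (Methods and analysis) and Study design {8} both call the trial double-blind, and so does the title of the randomization section. That section makes two broad claims: "all patients and staff will be oblivious to their group assignment", and "The group assignment will be withheld from all patients and anesthesiologists".

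It then describes who does what. Nurse anesthetists hand over the envelopes and "tell to prepare the items for the experiment based on group allocations". The next step is "Following anesthesia induction, the anesthesiologist may perform the various surgeries in accordance with the coded number". A second anesthesiologist records the intraoperative data and follows the patient to discharge.

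Unblinding {17b} adds an analysis in which the groups are at first known only as A and B. Follow-up has an investigator record drainage once a day on postoperative days 1–3. On transfusion, Data collection and management says: "The decision to use blood products such as fibrinogen, prothrombin complex, coagulation factors, and platelets will be made based on the TEG results".

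The aPRP collection section ends with: "The anesthesiologist decided to perform aPRP".

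**The concern.** A coded number can hide the allocation until the envelope is opened. It cannot hide a technique from the person performing it. If the two techniques can be told apart by sight, the claim that every anesthesiologist and all staff are unaware of the arm cannot be true.

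Two things are at stake. First, a report that repeats the double-blind label would tell readers that care during surgery was protected from knowledge of the arm when it was not. Second, allogeneic blood use depends on clinical decisions. It is a main objective in Study design {8} and a secondary outcome in the abstract. Those decisions can be influenced by knowing the arm, and coagulation products could plausibly affect drainage as well. The Background states a hypothesis in favour of blood separation, so any expectation has a direction.

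**Working it through.** No figure in the article bears on blinding, so the check sets the sections side by side.

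**1. Can the techniques be told apart?**

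| Feature | ANH | aPRP |
|---|---|---|
| Volume drawn | 8–10 mL/kg (General anesthesia) | "approximately 15–20 mL/kg whole blood collected prior to heparin administration" (aPRP collection) |
| Processing | no separation step described | centrifugal separation on a dedicated device |
| Red cells | kept within the whole blood | returned after collection (General anesthesia) |
| Storage | whole blood in a citrate bag | shaken, at room temperature |

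The draw ranges do not overlap. The aPRP draw is between 15/10 = 1.5 and 20/8 = 2.5 times the ANH draw. The Discussion itself says that separation needs special equipment and trained experts, and that ANH is simpler. The article describes no sham separation, no screening of the equipment and no separate unblinded team. The techniques are therefore plainly distinguishable to anyone who performs or watches them.

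**2. Who can be blinded, role by role?**

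| Role | Task in the article | Blinding |
|---|---|---|
| Nurse anesthetist | prepares items by allocation | not possible |
| Operating anesthesiologist | "the anesthesiologist may perform the various surgeries in accordance with the coded number" | not possible |
| Others in the operating room | present with the device and the stored product | not possible in practice |
| Second anesthesiologist | records data before and after collection and before and after return | not credible, since these are the moments when the technique is visible |
| Patient | anesthetized during collection | plausible |
| Investigator recording drainage | daily reading, days 1–3 | possible, but not stated |
| Statistician | analysis first coded A/B | plausible |

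**3. Do the stated safeguards close the gap?** Sealed envelopes protect concealment before assignment. The A/B coding protects the analysis. The blinding committee, as described, oversees the release of the codes. None of these reaches the people giving care. The recorder is also said to follow the patient until discharge, and the article does not say whether this is the person who records drainage. The text therefore does not secure blinding for the reading of the primary outcome.

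**4. What follows for transfusion?** TEG guidance limits discretion. The article does not say who orders blood products, where, or whether that person knows the arm. Bias here is possible, but it has not been shown and cannot be sized.

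**5. The closing sentence of aPRP collection.** Read alone, it says that a clinician chose aPRP. The sentence just before it concerns the end of bypass, transfusion of the collected blood, heparin neutralization and absence of bleeding, so it may refer only to the timing of return. The Patients, Enrolling {16c} and randomization sections all describe random assignment, and the last two say it is computer-generated. The sentence needs clarifying. The blinding contradiction stands without it.

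**The case against.** The best defence is that the label is loose wording in a condensed, imperfectly translated article, and that the protections that matter most are still in place. Patients are anesthetized, allocation is concealed in sealed envelopes, someone other than the operator records the data, the analysis is coded, one surgical team treats everyone, and an independent body monitors the trial. Drainage, which the abstract makes primary and the sample size rests on, is a measured volume and can be read blind. Much of this stands. Patient and analyst blinding are credible, and the exposed outcome that depends most on judgement is secondary in the abstract. But the article does not merely omit detail. It positively asserts that all staff and all anesthesiologists are unaware, and its own procedures rule that out.

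A reader might also infer two stronger points that the document does not support:

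- **That technique followed clinician choice, so that the comparison is confounded.** The only basis is one ambiguous sentence that follows text on reinfusion, set against three sections that state random assignment.
- **That every intraoperative blood product decision in the 160 patients was made by someone who knew the arm.** No section says who orders products or where. The absence of TEG thresholds is no finding either, since an article may leave them to the full protocol.

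**Conclusion.** The point holds for blinding. The operator and operating-room staff cannot be unaware of the arm, so the trial is not double-blind in the sense the article states. Confidence in this is high, because it rests only on the article's own account of the two techniques and of who performs them.

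Blinding of the patient and the statistician remains plausible, assuming that patients are not told their arm afterwards and that the A/B coding is kept until the analysis is done. Blinding of the drainage assessor is achievable but not stated.

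For allogeneic transfusion there is a plausible risk of bias, reduced by TEG guidance and not quantifiable from the article. A failure of randomization is not shown. The closing sentence of aPRP collection is an ambiguity to resolve.

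**What to change.** 1. Replace the double-blind claim in the abstract, Study design {8} and the randomization section with a list of roles. Blinded: patient, statistician and, where this is so, the drainage assessor. Not blinded: the operating anesthesiologist, nurse anesthetists and other operating-room staff.
2. From now on, assign the day 1–3 drainage readings to existing staff who were not in the operating room. Recruitment began on July 1, 2019, so this cannot be applied to patients already assessed. Report who read drainage for them and whether that person knew the arm.
3. Report allogeneic transfusion as an outcome whose decision-makers may have known the arm, and state that products were guided by TEG.
4. Reconcile the closing sentence of aPRP collection with the randomization sections. State that allocation alone determines the technique, and say what the sentence refers to.

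The cost is protocol wording, submitted to the ethics committee under Important protocol modifications {25}, and a reassignment of duties among existing staff. No extra patients are needed. The downside is that the trial can no longer be called double-blind, and drainage may have been assessed differently in earlier and later patients, which the report must disclose.

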#### Unblinding {17b}

A blinding committee is convened, which consisted of experts to oversee and guide the blinding process. At the end of the trial, after the completion of the locking library, in order to carry out the analysis, the first level of blinding, so as to know each subject as group A or B, but do not know the specific group A and B group operation. On the basis of primary blinding, statistical analysis is performed to clarify the difference between group A and group B. Secondary blinding is then performed to know the operation group information of each subject, to clarify whether it is the test group or the control group, and to further analyze the results of the clinical trial. The blinding results are recorded in a blinding form and confirmed and signed under the supervision of a blinding committee. Under the direction of a blinding committee, the outcomes of the blinding are documented in a blinding form and verified and signed.

The study will be overseen by an impartial data and safety monitoring body. The data will not be released until the final statistical analysis has been completed.

To minimize bias and avoid any influence of the surgeon on the results of the trial, all enrolled patients will be treated by the same surgical team.

## Interventions

### General anesthesia

All patients will receive general anesthesia as follows: induction with midazolam 0.05 mg/kg, etomidate 0.3 mg/kg, sufentanil 0.5 μg/kg, and cis-atracurium 0.2 mg/kg. The anesthesia machine is connected after tracheal intubation, with the tidal volume set at 6–8 mL/kg and the respiratory rate at 12 breaths/min. The intraoperative end-tidal CO_2_ pressure is maintained at 35–45 mmHg by adjusting the respiratory parameters. Anesthesia is maintained with continuous pumping of 4–8 mg/kg/h propofol, with sufentanil and cis-atracurium injections at regular intervals. After induction of anesthesia, a large-diameter catheter is placed in the patient’s right internal jugular vein. The red blood cells were reinfused back into the patient after collection, and the collected aPRP was infused back into the patient after extracorporeal circulation following neutralization of heparin with fisetin.

There is no universally accepted criterion for determining the ideal amount of whole blood to collect for ANH, which is sometimes established clinically by diluting the target hematocrit or blood volume. However, according to the 2019 expert agreement on the clinical treatment of autologous blood transfusion, the total volume for blood collection should be as follows: 10–15% of total blood volume, with an increase to 20–30% of total blood volume in rare instances or in patients with improved health status. Accordingly, autologous blood is taken from the internal jugular vein following anesthesia and central venous cannulation with a volume of 8–10 ml/kg and Hct > 30% before CPB in the ANH group, and acute isovolumic hemodilution with sodium acetate-Ringer solution is conducted. If the collected blood is required for extracorporeal circulation reasons, this test will exclude this case. Ringer’s acetate will be used as a volumetric substitute to maintain hemodynamic stability throughout the blood collection process at a ratio of 1:1.5 (volume replenishment). Previous studies used crystalloids at a ratio of 1:3, and a pre-study test demonstrated that a ratio of 1:1.5 provided safe and effective volume replacement. At the end of the procedure, the patient is returned to the cardiac surgical care unit with assisted ventilation with a respiratory ball.

A five-lead electrocardiogram, ambulatory blood pressure, oxygen saturation, end-expiratory CO_2_ pressure, near-infrared spectral cerebral oxygen saturation, and nasopharyngeal temperature will be monitored throughout the procedure and blood gas analysis and TEG will be performed regularly.

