### The treatment of non-adherence and missing data{20c}

If there is a clear violation of the protocol, the trial should be stopped, and the subject’s data should be blinded and not included in the final statistical results; if it can be adjusted in time and does not make a significant difference, the data set can be retained. If there are missing data cases, replacement of the data can be tried if necessary, based on the dataset’s characteristics and qualities.

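### Patients whose collected blood is needed for bypass are excluded after randomisation, apparently in the ANH arm only, with a risk of selection bias of unknown size and direction

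*Protocol article*

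**What the plan says.** Under General anesthesia, the article describes whole-blood collection for the control arm, "with a volume of 8–10 ml/kg and Hct > 30% before CPB in the ANH group". The next sentence reads: "If the collected blood is required for extracorporeal circulation reasons, this test will exclude this case".

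Two statements fix the timing. On allocation: "Groups will be chosen before patient admission". On collection: "autologous blood is taken from the internal jugular vein following anesthesia and central venous cannulation".

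For the experimental arm, the aPRP collection section says: "The collected whole blood will be divided into aPRP and red blood cells using an autologous transfusion system". It ends collection without any removal rule: "Blood collection was stopped when the target volume was reached". The General anesthesia section adds for this arm: "The red blood cells were reinfused back into the patient after collection".

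The section on non-adherence and missing data {20c} says that on a clear protocol violation "the subject’s data should be blinded and not included in the final statistical results". No section says that patients are analysed as randomised, or that the outcome data of the excluded cases enter the analysis.

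**The concern.** Randomisation protects the comparison only if the patients analysed are those allocated, or if any loss is unrelated to outcome. Here the loss depends on an event that follows allocation and the start of the intervention. The event is also part of how ANH plays out: the reserve is whole blood that bypass may call on, whereas in the aPRP arm the red cells have already gone back to the patient.

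Need for blood during bypass could plausibly be related to both outcomes that matter here: postoperative drainage (the primary objective in the Abstract) and allogeneic blood use (a main objective under Study design). If it is related, the ANH patients who remain are a selected group compared with an aPRP arm that was not selected in the same way. The estimated difference would then mix the effect of treatment with the effect of selection.

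**Working it through.** **1. Order of events.** Allocation (before admission) → anesthesia and central venous cannulation → ANH collection → possible need for the blood for bypass → exclusion. The trigger cannot precede allocation, so the rule is not an eligibility criterion.

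**2. Which arm.** The sentence names no arm. It directly follows the sentence that names the ANH group, and the aPRP section has no equivalent. ANH-only is therefore the likelier reading. If the rule were meant for both arms, it would still follow randomisation, and it would still fire differently, because whole blood is held back in one arm and platelet-rich plasma in the other.

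**3. The plan's own figures.** From Determination of sample size: 316 ± 102 mL (aPRP) and 378 ± 133 mL (control), 80 per group, power 80%, type I error 5%.
- Difference: 378 − 316 = 62 mL.
- Pooled SD: √[(102² + 133²)/2] = 118.5 mL.
- n per group, two-sided: 2 × (1.960 + 0.842)² × 118.5² / 62² = 57.4, so 58. The stated 80 is not reproduced at 80% power. This is a separate matter.
- Standard error at 80 vs 80: √(102²/80 + 133²/80) = 18.74 mL. Power = Φ(62/18.74 − 1.96) ≈ 91%. This is the reference below.

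**4. Illustration of the exclusion.** The share excluded, *f*, and the correlation, *r*, between selection and drainage are assumptions; the document gives neither. With normally distributed drainage and λ = φ(z)/(1 − f), where z is the (1 − f) quantile:
- shift in the ANH mean = r × λ × 133
- SD of retained ANH patients = 133 × √[1 − r²(zλ + λ²)]

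| f | r | λ | Shift (mL) | Share of 62 mL | Retained SD | ANH n | SE | Difference left | Power |
|---|---|---|---|---|---|---|---|---|---|
| 5% | 0.5 | 0.1086 | 7.2 | 12% | 129.8 | 76 | 18.75 | 54.8 | 83% |
| 10% | 0.5 | 0.1950 | 13.0 | 21% | 128.1 | 72 | 18.92 | 49.0 | 74% |

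Power uses the same normal formula as step 3; for example Φ(49.0/18.92 − 1.96) ≈ 74%. If there were no true difference, the 13.0 mL shift would raise the two-sided type I error from 5% to about 10.5%.

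**5. Other direction and null case.** The table takes the excluded patients to be the heavier bleeders. If they were the lighter bleeders, the apparent difference would grow to 62 + 7.2 = 69.2 mL or 62 + 13.0 = 75.0 mL, in favour of aPRP. If selection is unrelated to drainage (r = 0), there is no bias, only a small loss of power: about 89% with 10% of the ANH arm excluded (Welch t; 90.8% with none excluded).

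**The case against.** The strongest reply is that the rule may touch few patients and may be prognostically neutral. The document reports no frequency, no reasons and no outcomes for such cases. It also narrows one route to imbalance: the exclusion criteria already remove low hemoglobin and hematocrit, and ANH collection carries its own hematocrit condition before CPB. At 5% excluded with moderate selection, power stays above the planned 80%. All of this stands, and it limits the point to a risk of bias.

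Three stronger readings are tempting, and the documents do not support them.
- *Only control patients can be lost, while the aPRP arm keeps everyone.* The arm is inferred from where the sentence stands. Deaths after surgery (listed under the exclusion criteria) and clear protocol violations (section {20c}) can also remove aPRP patients.
- *The bias runs against aPRP and roughly halves the power.* That needs the excluded patients to be exactly the 10% with the highest drainage. The ANH mean then falls by 0.195 × 133 = 25.9 mL. Pairing that shift with the unchanged SD of 133 gives about 45% power, but cutting off the upper tail also reduces the SD to about 112, which gives about 54%. Even that is a perfect-selection limit, and the document gives no direction.
- *The damage cannot be undone.* The article does not say that the excluded patients' data go uncollected or are destroyed, so the analysis as randomised can still be secured.

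What remains is that no section brings these patients back into the analysis. An analysis plan that is not shown could not readily do so while the protocol takes them out of the trial.

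**Conclusion.** The point holds as a risk. The protocol article states a post-randomisation exclusion, apparently confined to the ANH arm, whose trigger may be related to drainage and transfusion. Its timing is clear from the text. Its restriction to ANH is the likelier reading, but rests on placement.

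Size and direction are not fixed by the document. Under the assumptions of 5–10% excluded, a correlation of 0.5 and normal drainage, the shift is about 7–13 mL, or 12–21% of the planned 62 mL. If the excluded patients bleed more, power falls from about 91% to 83–74%; if they bleed less, the aPRP benefit is overstated by the same amount; if they do not differ, nothing is biased. Because the direction is unknown and the remedy is cheap, the text should be changed before analysis.

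**What to change.** 1. Under General anesthesia, replace the exclusion sentence. Patients whose collected blood is used during bypass stay in the trial, are followed for drainage and transfusion like all others, and are analysed in the group to which they were randomised. Use of the blood is recorded as an intercurrent event.
2. Amend the section on non-adherence {20c} at the same time, so that neither this event nor other protocol deviations remove a patient from the primary analysis. Changing the first sentence alone may achieve nothing, since these patients could be classed as violators and dropped there.
3. Confine any exclusion to a labelled sensitivity analysis, with the same rule in both arms and the number excluded reported per arm.

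The cost is an edit to two sections and the ethics submission that the article requires for modifications. No extra patients or procedures are needed, since drainage is already recorded daily on postoperative days 1–3 and transfusion is already an outcome. The downside is that the estimate becomes the effect of the assigned strategy, not of completed ANH. The clinical decision to use the blood is unchanged.
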